#### Potential modifiers of treatment effect

Whiplash is a complex and heterogeneous condition and there is growing evidence to suggest that there is a subgroup of people who present soon after injury with altered sensory (mechanical and thermal) and psychological states; it is likely that these people are at an increased risk of developing persistent symptoms [28]. The following potential treatment effect modifiers will be measured in order to investigate whether they can predict those more likely to respond to treatment:

- Cold pain threshold will be measured over the cervical spine using a Thermotest System (Somedic AB, Sweden) [2].

- Pressure pain threshold will be measured over the cervical spine and the tibialis anterior using a Pressure Algometer (Somedic AB, Sweden) [2].

- Posttraumatic stress symptoms will be evaluated using the Impact of Events Scale [29] and the modified Post Traumatic Stress Diagnostic Scale [30]. Both are 15-item questionnaires used to assess posttraumatic stress symptoms that are related to a specific event.

- Signs and symptoms of catastrophising will be evaluated using the Pain Catastrophising Scale, a 13-item questionnaire developed to assess three components of catastrophising: rumination, magnification, and helplessness [31].

- The origin of participant's pain will be pain evaluated using the Self-report Leeds Assessment of Neuropathic Symptoms and Signs (S-LANSS) [32], a 7-item scale developed to identify neuropathic pain, as distinct from nociceptive pain.

### Data analysis

#### Effectiveness of the comprehensive exercise program

Intention to treat analyses will be used, exclusively, and will be conducted by an investigator who is blinded to group allocation. In the primary analysis the effect of treatment will be assessed separately for each outcome using linear mixed models with time as a repeated factor. The model will account for correlation over time within participants, correlation within clinics and potential confounders (e.g. important prognostic factors). Estimates of the effect of the intervention will be obtained by constructing linear contrasts to compare the mean change in outcome from baseline to each time point between the treatment and control groups, with adjustment for the other variables.

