### Randomisation

A computer-generated randomisation sequence, stratified for recruitment site (Sydney and Brisbane), will be produced prior to commencement of the trial by an independent researcher. Randomisation will occur immediately following the baseline assessment by opening the next sealed opaque envelope. Participants will be considered to have entered the study at the time that the envelope is opened.

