#### Comprehensive exercise program

Participants will receive twenty, one-hour individually tailored and supervised exercise sessions over a 12 week period. Exercise sessions will be delivered at physiotherapy clinics by physiotherapists trained to deliver the comprehensive exercise program. Figure 2 provides an overview of the program.

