#### Sample size

This study has been designed to detect clinically important interaction effects for the potential treatment effect modifiers. There will be sufficient power to detect the following effects: 2 units on the 0-10 pain intensity scale (estimate for SD = 2.00), 1.5 units on the 0-10 Patient Specific Functional Scale (estimate for SD = 1.5), 30 units on the 0-130 Whiplash Disability Questionnaire (estimate for SD = 30), 2.0 units on the -5 to +5 Global impression of recovery scale (estimate for SD 2.0), 6 units on the 0-50 Neck Disability Index (estimate for SD = 5.6), 15 points on the 0-100 SF36 physical summary score (estimate for SD = 10.0) and 15 points on the 0-100 SF36 mental summary score (estimate for SD = 11.0). However, the study is powered to detect main effects of half this size.

Standard deviation estimates have been taken from previous trials that recruited a similar patient cohort [16,17,24]. With specifications of alpha = 0.05, power = 0.80 and allowing for up to 10% loss to follow-up and 10% treatment non-compliance, a sample size of 86 participants per group will allow us to detect an interaction effect size equal to 1.0 times the SD as specified above and a treatment main effect of 0.5 SD.

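### The stratification factor, recruitment site, is not named in the primary mixed model; naming site and site-by-time, and adjusting for baseline, would be a minor improvement at almost no cost

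*Protocol article*

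**What the plan says.** The Randomisation section of the protocol article fixes one stratification factor: "A computer-generated randomisation sequence, stratified for recruitment site (Sydney and Brisbane"). No other factor, and in particular not clinic, restricts the allocation.

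Under Data analysis (Effectiveness of the comprehensive exercise program), each outcome is analysed separately "using linear mixed models with time as a repeated factor". The terms are then described: "The model will account for correlation over time within participants, correlation within clinics and potential confounders (e.g. important prognostic factors"). The treatment effect is taken from linear contrasts that "compare the mean change in outcome from baseline to each time point between the treatment and control groups, with adjustment for the other variables".

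Site does not appear by name among these terms. The covariate part is open-ended, so site is not excluded either. On clinics, the Comprehensive exercise program section says: "Exercise sessions will be delivered at physiotherapy clinics by physiotherapists trained to deliver the comprehensive exercise program". The number of clinics, their cities and the clinic assigned to a control participant are not given.

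**The concern.** A factor that restricted the randomisation belongs in the analysis because of the design, whether or not someone later judges it prognostic. If it is left out and the outcome differs between strata, that difference stays in the residual. The treatment estimate remains unbiased, but its model standard error is larger than its true sampling error, and part of the benefit of stratifying is lost.

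A difference between the cities is plausible. The Study Population section describes recruitment partly through two regulators, one for each state's compulsory injury insurance scheme. The primary model names clinic, a factor that did not constrain allocation, and does not name site, the factor that did.

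At stake is a small amount of precision. There is no risk of bias or of excess false positives.

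**Working it through.** **Inputs from the protocol article.** Two strata (Randomisation); model terms and change-from-baseline contrasts (Data analysis); 86 per group, alpha 0.05, power 0.80, 10% loss, 10% non-compliance, main effect 0.5 SD (Sample size).

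**Assumptions not in the document.** Two-sided alpha; cities of equal size; allocation balanced within each city; the size of any difference between cities.

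**1. The plan's own sample size.** n per group = 2 × ((1.96 + 0.84)/0.5)² = 62.8. Dividing by 0.90 for loss and by 0.90² for dilution by non-compliance gives 62.8/(0.90 × 0.81) = 86.1, which reproduces "a sample size of 86 participants per group". The calculation contains no site or clinic variance, so naming site does not change it.

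**2. A constant city difference in level.** If one city's mean is higher by the same amount at every visit, that amount is in both the follow-up and the baseline value and drops out of the change. Even without that cancellation, the clinic term does most of the work. A simulation used a single follow-up outcome, 154 analysed, five clinics per city and 4,000 runs per setting:

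| City difference (SD) | Model SE, neither term | Model SE, clinic intercept | Model SE, clinic + site | Type I error, neither / clinic / clinic + site |
|---|---|---|---|---|
| 0.25 | 0.162 | 0.161 | 0.161 | 0.048 / 0.051 / 0.050 |
| 0.5 | 0.166 | 0.163 | 0.161 | 0.044 / 0.050 / 0.050 |
| 1.0 | 0.180 | 0.165 | 0.161 | 0.029 / 0.048 / 0.052 |

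With the clinic intercept, the model SE tracks the empirical SE (0.163 v 0.164 at 0.5 SD; 0.165 v 0.166 at 1.0 SD). Adding site narrows the SE by about 1% at 0.5 SD and 2% at 1.0 SD.

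**3. A city difference in change.** This does not cancel. A clinic intercept that is constant over time largely cannot absorb it either, because it models level and not change. Let d be the city difference in units of the within-city SD of change. Two equal cities add d²/4 to the residual variance, while balance within cities keeps it out of the true sampling variance. Hence:

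- SE inflation k = √(1 + d²/4)
- actual type I error = 2 × (1 − Φ(1.96k))

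| d (assumed) | k | Type I error |
|---|---|---|
| 0.3 | 1.011 | 0.047 |
| 0.5 | 1.031 | 0.043 |
| 0.8 | 1.077 | 0.035 |

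**4. Check with the clinic term in place.** A second simulation used baseline plus one follow-up, 160 participants, five clinics per city, unstructured within-person covariance, a clinic random intercept and 400 runs per setting. It compared the model without site to the model with site-by-time:

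- d = 0.5: SE 0.163 v 0.158 (3% larger); type I error 0.040 v 0.045.
- d = 0.8: SE 0.169 v 0.158 (7% larger); type I error 0.028 v 0.048.

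Monte Carlo error on these type I figures is about 0.01, so they agree with step 3.

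**5. Baseline.** With equal variances and baseline–follow-up correlation r, the SE of a pure change contrast is proportional to √(2(1 − r)), and that of a baseline-adjusted contrast to √(1 − r²). The ratio is √(2/(1 + r)). For assumed r = 0.7 it is √(2/1.7) = 1.08; for r = 0.3 it is √(2/1.3) = 1.24. The change contrast therefore has an SE about 8% to 24% larger.

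**The case against.** The strongest reply is that nothing in the article is wrong. The covariate list is open and could include site; an article condenses the full protocol; and the exact list may stand in an analysis plan that is not shown. Each clinic presumably lies in one city, so a clinic term carries most of a city difference. The Quality assurance section has each physiotherapist audited on one treatment and one advice session, which suggests that control participants could be linked to clinics too. The contrasts are on change, and any remaining error is conservative.

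Most of this stands. Site is unnamed, not shown to be excluded, and validity is not threatened. Two parts do not stand. An open list commits to nothing, whereas a stratification factor should be fixed by design. And the protection from clinic concerns mainly the difference in level, which already cancels. A clinic-by-time effect would absorb much of a difference in change, but the article does not specify one. If controls have no clinic link, the clinic term protects less.

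Two stronger readings are tempting. A reader might infer that the standard errors ignore the restriction imposed by stratification. The documents do not support that, given the clinic term, the change contrasts and the open list. A reader might also infer that power falls below 0.80. That would follow only if the planning SD were a within-city SD. The Sample size section takes its SDs from previous trials and mentions no site adjustment. If they are total SDs, power without site is Φ(0.84k), or 0.80, 0.81 and 0.82 for d = 0.3, 0.5 and 0.8, and adjustment is an added gain.

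**Conclusion.** The point holds as a minor one. Allocation is stratified by site, the description of the primary model does not name site, and the contrasts are on change from baseline. Inference remains valid. For assumed city differences in change of 0.3, 0.5 and 0.8 SD, the SE would be about 1%, 3% and 8% too large and the test slightly conservative; the planned sample size is unaffected. These figures rest on equal-sized cities, balance within city, two-sided alpha and a clinic term that is a random intercept constant over time. With no city difference in change, there is essentially nothing to gain from site.

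Adjustment for baseline probably brings the larger gain in precision. Its size depends on a correlation that the article does not give.

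**What to change.** In the Data analysis section on effectiveness, state that recruitment site and site-by-time are fixed effects in the mixed models, in addition to the clinic correlation.

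State also that the follow-up comparisons are adjusted for the baseline value of the outcome. Baseline is currently a repeated response, so it cannot simply be added as a covariate as well. Choose one of two forms:

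- baseline as a covariate, with only 14 weeks, 6 months and 12 months as responses; or
- baseline kept as a response, with its mean constrained to be equal between arms.

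The cost is a sentence or two. Site and site-by-time use one degree of freedom per response time: three in the first form, four in the second. No extra data are needed, since site and baseline outcomes are already recorded, and the sample size does not change.

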### Outcome assessments

Participants will be evaluated by an assessor who is unaware of group allocation at 14 weeks, 6 months and 12 months after randomisation.

The baseline assessment will involve the collection of the participant's demographic data including, information about their whiplash symptoms, accident history, medical history, current medications, previous investigations and treatment, employment and compensation status. The primary and secondary outcomes as well as potential effect modifiers will be measured at baseline and all other assessment time points.

The *primary outcome *is the average pain intensity over the last week as measured using a 0 to 10 point numerical rating scale [21]. *Secondary outcomes *are:

- Average pain intensity over the last 24 hours measured using a 0 to 10 numerical rating scale [21]

- Patient's global impression of recovery measured on a numerical rating scale from -5 (vastly worse) to +5 scale (completely recovered) [22].

- Perceived disability measured using the Neck Disability Index a 10-item questionnaire designed to measure neck specific disability [23] and the Whiplash Disability Questionnaire: 13-item whiplash-specific measure of disability [24].

- Health related quality of life measured using the SF-36 [25].

- Cervical range of movement using an inclinometer [26].

- Perceived function measured using the Patient-Specific Functional Scale: 3-item patient-generated measure of function [27].

Adverse effects of treatment will be identified using open-ended questioning at the 14 week follow-up assessment only. In addition to the primary and secondary outcomes, economic outcomes will be collected to assess the cost-effectiveness of the comprehensive exercise program. Details of the cost-effectiveness analysis will be reported in a separate manuscript.

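### The treatment effect is defined as a difference in change from baseline, which on its plain reading is less precise than a baseline-adjusted difference from the same data

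*Protocol article*

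**What the plan says.** Under Data analysis, in the subsection on effectiveness, the protocol article analyses each outcome "using linear mixed models with time as a repeated factor". On the effect itself it says: "Estimates of the effect of the intervention will be obtained by constructing linear contrasts to compare the mean change in outcome from baseline" to each follow-up between the arms, adjusted for the other variables in the model. Those variables are correlation within clinics and "potential confounders (e.g. important prognostic factors"; no covariate is named. The text does not list the outcome's own baseline score as a covariate and does not say that the arms share a common baseline mean.

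Under Outcome assessments, the primary outcome is "average pain intensity over the last week as measured using a 0 to 10 point numerical rating scale". The same section confirms that the baseline scores will exist: "The primary and secondary outcomes as well as potential effect modifiers will be measured at baseline and all other assessment time points".

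Under Sample size, the interaction effect for pain is given as "2 units on the 0-10 pain intensity scale (estimate for SD = 2.00", and main effects of half that size are claimed. The target of 86 per group is derived "With specifications of alpha = 0.05, power = 0.80 and allowing for up to 10% loss to follow-up and 10% treatment non-compliance". The section says that SDs come from earlier trials, but not whether they are SDs of the score or of its change. It gives no baseline to follow-up correlation.

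**The concern.** A contrast in change from baseline needs baseline as one level of the repeated response. If each arm has its own free baseline mean, the contrast with complete data is simply the difference between arms in mean change score.

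Randomisation makes the true baseline means equal, so an observed baseline difference is chance. The change score subtracts that difference in full. Baseline adjustment subtracts only the part that predicts the follow-up score. The change score therefore carries extra noise: intervals are wider than they need to be, and the estimate over-corrects for whatever chance imbalance occurs. At stake is precision on every outcome at every follow-up, in a trial whose size was set at the stated power with no margin.

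**Working it through.** **Inputs from the protocol.** Sample size section: 86 per group, alpha 0.05 (taken as two-sided, which reproduces the sample size), power 0.80, main effect 0.5 SD, 10% loss, 10% non-compliance, pain SD 2.00.

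**Assumed.** The correlation r between baseline and follow-up, shown over 0.3 to 0.7; equal baseline and follow-up SDs unless stated; no correlation within clinics.

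**Step 1: reproduce the sample size.**
- n per group = 2 × (1.960 + 0.842)² / d².
- At d = 0.5 this gives 62.8, so 63.
- Non-compliance of 10% dilutes d to 0.45, which gives 77.5.
- Dividing by 0.9 for loss gives 86.1, matching the stated 86.
- With 86 × 0.9 = 77.4 analysed per group and d = 0.45, power is 0.799.
- The formula uses one SD and has no correlation term.

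**Step 2: compare the variances.** Let s0 and s1 be the baseline and follow-up SDs.
- Change score: s1² + s0² − 2·r·s0·s1.
- Baseline-adjusted (large sample): s1²(1 − r²).
- Difference: (s0 − r·s1)², which is never negative for any r or any pair of SDs.
- With s0 = s1 the two are proportional to 2(1 − r) and 1 − r², so the ratio is 2/(1 + r).

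**Step 3: power, if 2.00 is the SD of the score.** Power = Φ(0.45 / √(2v/77.4) − 1.96), with v = 2(1 − r) or 1 − r².

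| r | v, change | v, adjusted | Ratio | Power, change | Power, adjusted |
|---|---|---|---|---|---|
| 0.3 | 1.40 | 0.91 | 1.54 | 0.66 | 0.84 |
| 0.4 | 1.20 | 0.84 | 1.43 | 0.72 | 0.86 |
| 0.5 | 1.00 | 0.75 | 1.33 | 0.80 | 0.90 |
| 0.6 | 0.80 | 0.64 | 1.25 | 0.88 | 0.94 |
| 0.7 | 0.60 | 0.51 | 1.18 | 0.95 | 0.98 |

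**Step 4: vary the assumptions.**
- If 2.00 is the SD of change, v = 1 for the change contrast whatever r is, and its power is the stated 0.80.
- If neither loss nor non-compliance occurs (86 per group, d = 0.5), change-score power falls below 0.80 only when r is below about 0.315.
- If the baseline SD is 0.75 of the follow-up SD, change-score power is 0.76 at r = 0.3 and 0.81 at r = 0.4.

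**Step 5: confirm which estimator the wording gives.** One simulated data set was analysed (86 per group, four time points, r = 0.3, complete data, SD units).

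| Analysis | Estimate | SE |
|---|---|---|
| Group-by-time mixed model, free baseline means | −0.506 | 0.175 |
| Raw difference in mean change | −0.506 | not computed |
| Follow-up regressed on arm and baseline | −0.465 | 0.144 |
| Mixed model, equal baseline means | −0.463 | 0.140 |

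Adding the baseline score to the first model as a main effect left its estimate and SE unchanged at −0.506 and 0.175. A main-effect term contributes equally at every time point and cancels from a contrast between two of them.

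**The case against.** The strongest reply is that the protocol does not rule out baseline adjustment. It adjusts for prognostic factors that it does not name, and the baseline score could be one. The same change contrast is also fully efficient if the model constrains baseline means to be equal, so the wording is compatible with a good analysis. A fuller protocol or an SAP may settle it.

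Part of this stands. The text excludes neither option, so a reader who infers that the trial has rejected baseline adjustment goes further than the document does. But the prognostic-factor argument does not rescue the contrast as written, because a main-effect covariate cancels from it. Only an equal-baseline constraint, a covariate-by-time term, or moving baseline to the covariate side recovers the precision, and none of these is stated. The contrast itself is stated, so this is a comment on a chosen estimator and not on an omitted detail.

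A reader might also infer that the trial is underpowered. The document does not support that. In the calculation above, a shortfall needs 2.00 to be the SD of the score and r to be below 0.5, with equal SDs over time and the full planned loss and dilution. The document establishes none of these. The entry criterion of at least moderate pain or activity limitation may narrow the baseline spread, which lessens the shortfall at a given r; it could also lower r, so the net direction is unknown.

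Finally, difference in change is a standard estimator, and under randomisation it is unbiased with valid type I error. That stands in full.

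**Conclusion.** The point holds as one of efficiency. On the plain reading, the stated contrast is a change-score comparison, and its large-sample variance is never smaller than that of a baseline-adjusted estimate. That ordering needs no assumption about r. Its size does: under the assumed range of r from 0.3 to 0.7, with equal SDs, the variance ratio runs from 1.54 down to 1.18, so the adjusted standard error is about 19% to 8% smaller (1 − √((1 + r)/2)).

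The consequence for power is conditional. The planned 86 per group reproduces, and above r = 0.5 the change contrast exceeds the planned power even if 2.00 is the SD of the score. No validity error and no power shortfall has been demonstrated. The figures ignore correlation within clinics, and the exact equality with raw change scores applies to complete data.

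**What to change.** In the effectiveness subsection, define the effect as the adjusted between-group difference at each follow-up, from a linear mixed model of the follow-up scores with the baseline value of that outcome and its interaction with time as covariates. Alternatively, keep baseline as a response, constrain its mean to be equal across arms, and retain the change contrast. If one of these is already intended, one sentence saying so is enough.

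In the Sample size section, state whether each SD is that of the score or of the change and, if an estimate is available from the earlier trials, give the baseline to follow-up correlation.

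The cost is wording only: the baseline scores are already to be collected, and no visit, measurement or participant is added.

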#### Potential modifiers of treatment effect

Effect modification will only be assessed for the primary outcome of average pain intensity over the last week. This will be done by including a predictor-by-treatment group-by-time interaction term to the mixed models analyses.

#### Sample size

This study has been designed to detect clinically important interaction effects for the potential treatment effect modifiers. There will be sufficient power to detect the following effects: 2 units on the 0-10 pain intensity scale (estimate for SD = 2.00), 1.5 units on the 0-10 Patient Specific Functional Scale (estimate for SD = 1.5), 30 units on the 0-130 Whiplash Disability Questionnaire (estimate for SD = 30), 2.0 units on the -5 to +5 Global impression of recovery scale (estimate for SD 2.0), 6 units on the 0-50 Neck Disability Index (estimate for SD = 5.6), 15 points on the 0-100 SF36 physical summary score (estimate for SD = 10.0) and 15 points on the 0-100 SF36 mental summary score (estimate for SD = 11.0). However, the study is powered to detect main effects of half this size.

Standard deviation estimates have been taken from previous trials that recruited a similar patient cohort [16,17,24]. With specifications of alpha = 0.05, power = 0.80 and allowing for up to 10% loss to follow-up and 10% treatment non-compliance, a sample size of 86 participants per group will allow us to detect an interaction effect size equal to 1.0 times the SD as specified above and a treatment main effect of 0.5 SD.

